c Payable net gains are capped at CA $500. This amount is therefore CA $500+ money inserted in the EGM by the participant during the gambling session.

d Money gained by the participant that they did not have before the gambling session.

e The amount inserted in the EGM is returned to the participant (CA $60 in all examples) + stipulated compensation.

Third, the gambling session’s duration is limited to 2 hours. The gambling session starts when the participant inserts money for the first time in the EGM. Breaks during the gambling session are permitted (eg, using the restroom, buying snacks from the bartender or barmaid, etc) but are included in the 2-hour time limit. If the participants have not yet ended their gambling session upon reaching the 2-hour time limit, they are offered to take a short break to answer some questions. They then proceed to the postexperiment phase. If the participant insists on continuing to play or tries to quit hastily (eg, because they are angry about losing money), they are prematurely debriefed before proceeding with the postexperiment phase.

Fourth, unbeknownst to them, participants are monitored through a secret camera hidden in the ceiling during their gambling session. Their gambling behavior is also recorded from the EGM they play on.

#### Intake Interview

The intake interview collects information on basic sociodemographic factors, gambling behaviors on EGMs (past 12 months), general level of fun while playing EGMs (past 12 months), and perceived self-control while playing EGMs. Participants then schedule a gambling session to be done in our laboratory on the university’s campus. While free to choose any date and time they wish, participants are encouraged to select a moment that fits their usual gambling habits. There is no maximum or minimum time limit between the intake interview and the gambling session in the laboratory. Sessions are usually scheduled days to weeks after the intake interview.

### Experimentation Phase

#### Randomization

Blocks are size 4 and strata are divided on problem gambling severity using PGSI categories. Randomization was done using RANDOM.ORG’s list randomizer tool. The list within each block, “1, 1, 0, 0” (where “1” is experimental condition and “0” is control), was randomized 20 times for each PGSI category, excluding the probable pathological gambling category (see Figure 2). This arrangement of 80 places for the three lowest PGSI categories allows for any combination of levels of problem gambling among recruited participants while preventing major imbalance between the 2 groups on this characteristic.

**Figure 2. F2:**
[figure not shown]
Randomization procedure. PGSI: Problem Gambling Severity Index.

Allocation is done just before the participants arrive at the laboratory, on the day of the experiment. Participants are allocated to the first available spot from the top of the randomized list corresponding to their PGSI category (see Figure 3). Participants who complete the intake interview but do not show up at the scheduled appointment vacate their spot on the list. They may then be reassigned depending on whether they reschedule another gambling session. Meanwhile, the vacated spot becomes available for another participant who fits the same profile. The moment participants present themselves to the laboratory, their spot on the list cannot be reallocated, even if they desist later in the process.

**Figure 3. F3:**
[figure not shown]
Allocation procedure. PGSI: Problem Gambling Severity Index; NPG: nonproblem gamer; LRG: low-risk gambler; Condition 1: Experimental; Condition 2: Control.

#### Concealment of Allocation and Blinding

While participants in the experimental group should notice the novel prevention pop-up messages, for all they know before debriefing, there is no “assignment” per se. This is because the study is presented as an opinion survey about the realism of the bar replica and the gambling session in it. No instruction suggests any type of comparison between conditions. Therefore, participants would not be aware that there are 2 different groups, nor that this study tests the effects of prevention pop-up messages.

Note that masking becomes “open label” after debriefing. Indeed, after being informed of the true goals of this study, participants are easily able to determine in which group they were allocated based on what occurred during their gambling session. Regardless, gambling behaviors are recorded before debriefing and would not be affected by unmasking. There is no functional way to mask group assignment to the research team. However, the randomization procedure ensures that allocation is purely random.

#### Gambling Session in the Laboratory

There is only a single participant at a time in the laboratory for the gambling session. Each participant arrives at the lab at a scheduled appointment. Then, a research assistant greets the participant and proceeds to refresh their memory about the important aspects of the study. The participant is then brought to a room replicating a typical bar with EGMs (eg, subdued light, music, bar paraphernalia, fake liquor on display, etc; see Figures4  5 and Multimedia Appendix 1 for additional images).

**Figure 4. F4:**
[figure not shown]
Bar environment—electronic gambling machines and lounge.

**Figure 5. F5:**
[figure not shown]
Bar environment—bar paraphernalia and music TV.

Upon entering the bar, the participant is greeted by another member of our research team who plays the role of bartender operating the cash register and ensuring the general safety of the session. The addition of this bartender is done to improve the general realism of the gambling setting. The bar replica has 3 EGMs, but only 1 can be played on and used to show the prevention pop-up messages. The other 2 EGMs are turned on for ambiance purposes, but their money collectors are disabled. Limiting play to only a single EGM eases the recording of gambling behaviors and proper showing of the prevention messages. The participant is told that the 2 unusable EGMs are awaiting servicing due to a malfunction with their money collector.

The participants are free to do as they please (eg, play EGMs, buy chips and nonalcoholic beverages, relax in the bar, etc). They are allowed to leave the bar if they need to go to the bathroom or smoke. They are accompanied by the bartender if they elect to do so. The reference time point of the experiment (ie, T+00:00:00) starts when the participant inserts money for the first time in the EGM. Note that breaks in play, no matter the motive, do not stop the experiment timer regarding the duration limit.

While the participant is in the bar, a second research assistant observes from an adjacent room and is responsible for recording all gambling behaviors using a computer connected to the EGM and operating the pop-up messages presentation schedule (see Figure 6). A live-feed spy camera disguised as a smoke detector is used to observe gambling-related behaviors that cannot be recorded by the EGM’s computer (eg, taking a break).

**Figure 6. F6:**
[figure not shown]
Observation post.

The session ends when one of the two following conditions is met: (1) the participant expresses, without ambiguity, that they wish to end the experiment, and (2) T+02:00:00 is reached. The procedure may slightly vary depending on how the gambling session ends. Under normal circumstances, the participants end their session by themselves, before reaching the T+02:00:00 time limit. In this scenario, the procedure continues normally, as described in the postexperimentation phase section. Alternative scenarios are:

Alternative scenario 1: The participant reaches the T+02:00:00 time limit and continues to play. The member of the research team, playing the role of bartender, interrupts the participants and suggests taking a pause to answer some questions. If the participant agrees, the procedure continues normally, as described in the postexperimentation phase section. Unbeknownst to them, they will not be allowed to resume gambling after said questions.Alternative scenario 2: Same as “Alternative scenario 1,” but the participant refuses and insists on continuing to play, and debriefing is done on the spot to end the play session. All questionnaires presented in the postexperimentation phase section are done, but contrary to the normal scenario, evaluation of participants’ perception of the realism of the bar replica and of the gambling session is done after debriefing.Alternative scenario 3: The participants try to hastily quit the laboratory before we get a chance to debrief them (eg, because they are angry about losing a lot of money and do not wish to participate any longer). In this case, debriefing is done early to prevent them from quitting without receiving all the information to make an informed decision about their participation. All questionnaires presented in the postexperimentation phase section are done, but contrary to the normal scenario, evaluation of participants’ perception of the realism of the bar replica and of the gambling session is done after debriefing.

#### Active Control Group: Regular Gambling Session

This condition is designed to closely replicate a typical gambling session in a natural setting.

##### Electronic Gambling Machines (EGMs)

Gambling is done on fully functional and unaltered EGMs, model IGT GL20. This is the model currently in use in Quebec, Canada, the location where this study is conducted. The wins and losses sequence is fully randomized and not determined beforehand. The payout rate is the same as what is prescribed by law (92%). These machines come equipped with basic responsible gambling features, the 2 main ones being a mandatory time limit reminder and a submenu containing responsible gambling information.

##### Mandatory Time Limit Reminder

The mandatory time limit reminder is activated either when (1) the previous time limit is up or (2) the player bank meter reaches CA $0. When the previous time limit is up, a pop-up takes up the upper third of the play screen and requires the player to set a new time limit using one of 5 choice buttons (first four buttons: 15, 30, 45, or 60 minutes; fifth button: cash out, which prints a receipt and ends the gambling session; see Figure 7). As the EGM cannot track who is playing, there are no limits on consecutive gambling sessions. When the player’s bank meter reaches CA $0, the pop-up described above appears as soon as new money is inserted in the EGM, no matter if the previous time limit is up or not.

**Figure 7. F7:**
[figure not shown]
Mandatory time limit reminder.

##### Responsible Gambling Information

A submenu accessed through a button on the main touch screen opens a window, which contains basic information on randomness and responsible gambling advice. The information is presented in small white font on a black background (see Figure 8 for an example and Multimedia Appendix 2 for a complete overview).

**Figure 8. F8:**
[figure not shown]
Responsible gambling information.

##### Food Purchases and Money Withdrawals

A payment terminal allows for buying nonalcoholic beverages (soft drinks or coffee) and chips during the experimentation. This is done to enhance the realism of the bar setting. It also allows for real cash withdrawal from a bank account during a gambling session. Quebec’s code of conduct for EGM commercialization prohibits retailers from having an ATM near their EGMs. It also prohibits them from lending money to consumers or withdrawing cash for them to gamble. However, this rule is not always easy to enforce in practice. For this study, participants are allowed to withdraw from their bank account if they ask by themselves. This option is not communicated upfront to them.

### Experimental Group: Regular Gambling Session With Prevention Pop-Up Messages

This condition is the same as the active control group with the addition of prevention pop-up messages delivered during the gambling session on a fixed presentation schedule.

#### Prevention Pop-Up Messages

Messages are shown full screen on the EGM’s play screen on a fixed presentation schedule from the moment the participant inserts money for the first time in the EGM (ie, T+00:00:00). The first message is shown at T+00:10:00. Messages block the play screen for 15 seconds before automatically closing. This presentation frequency is thought to be a good compromise between a very high and potentially annoying frequency (eg, [21,48]) and a very low frequency where only a few participants are exposed (eg, [23]). The first message is presented sooner than the others so that every participant has a decent chance to see at least one. The subsequent presentation schedule is modeled on Schrans et al [50]. While it would have been ideal that messages stay on until participants close them, this was not possible due to hardware limitations on the EGMs’ part. The 15-second presentation duration was chosen based on the mean reading speed of a typical francophone adult [76], so participants have enough time to read the messages.

Up to 4 different messages are presented during the gambling session. Order is determined by sortition without replacement. Variations were introduced to counter the possible habituation effect [19,64]. All messages follow the same template (see Textbox 2 and Figure 9 for an example and see Multimedia Appendix 3 for every message used in the study).

Textbox 2.Prevention pop-up messages template.The message is written in black characters on a white box to maximize text-background contrast.The message box is placed on a blue background, which matches the EGMs’ color palette. This is done so that messages appear native to the EGMs, not something introduced for a study. The background pattern behind the message box directs the eye toward the message. The signal word “Attention!” (ie, the French translation for “Caution!”) is used conjointly with a warning pictogram (yellow triangle containing an exclamation mark). The signal word is written in capital letters.The bulk of the messages comprised 4 concise statements: The first statement is the time spent gambling since the beginning of the session. This portion is a factual statement to ground the participant in the present. The second statement is a warning that gambling could lead to serious monetary loss. This is a realistic risk associated with gambling. We choose to warn about monetary harms because they are relevant to every gambler (anyone can experience betting too much money, and this can have consequences even after a single session). The third statement is a self-appraisal question about current gambling behavior. This is the only part of the message that changes across versions. There are 4 different variations on this question. Self-appraisal questions drive participants to develop self-determined motivation and goals regarding their gambling behavior. The fourth statement is a simple piece of advice that a break could help choose what is best for oneself. This advice aims to foster participants’ self-efficacy sentiment, enabling them to act in a way to protect themselves [77,78].Just below the message is a countdown indicating the time left before the message closes. This is to reassure participants that the message is not a bug of the EGM and that the only thing required of them is to wait and pay attention.The province’s Health Department logo is shown in the lower right corner as a more neutral and expert endorsement of the messages. From a general standpoint, the more a source is considered expert and trustworthy, the more a message is susceptible to having an effect [79]. In gambling, Munoz et al [80] found that the participants trusted a source that gave more attention to prevention messages from a perceived independent source (governmental organization) than from a source perceived as having a conflict of interest (org. funded by the local gambling operator). Furthermore, Lemarié and Chebat [81] reported that antigambling ads led to more gambling when coming from a gambling operator.

**Figure 9. F9:**
[figure not shown]
The prevention pop-up message, as displayed on the electronic gambling machine (EGM).

.

Note that due to hardware limitations on the EGMs’ part, the prevention messages presented only alter what is shown on the play screen (they fill the screen completely, hiding the game), but cannot pause the game per se. The EGMs’ buttons, sound, and music are still operational while the message is shown.

### Postexperimentation Phase

The participant is brought in a separate office after the end of the gambling session for a series of questionnaires (outcomes listed in “Secondary Outcome” and “Other Outcomes” sections) which are, in order:

Evaluation of participants’ perception of the realism of the bar replica and of the gambling session.Evaluation of participants’ ability to recall prevention pop-up messages. This includes multiple tasks of free recall (eg, describing the pop-up messages from memory) and cued recall (eg, selecting from a list the pop-up messages that were seen during the gambling session).Evaluation of participants’ cognitive and emotional response to prevention pop-up messages.Evaluation of protocol credibility (ie, if the participant really believed they were gambling their own money and were really risking their own money).

These questionnaires are comprised of Likert scales, multiple-choice questions, and open-ended questions. Contrary to more standard qualitative designs, open-ended question responses are not recorded in an audio format, nor are they transcribed verbatim [82]. Instead, the interviewer takes notes, which the participant can see on a computer screen. Participants are then asked to confirm that the interviewer’s notes accurately reflect their opinion. It has been suggested that note-taking is superior to audio recording for obtaining qualitative data [83].

Debriefing about the true goals of the study and final validation of consent to participate in the study are done between the evaluation of participants’ perception of the realism and the evaluation of participants’ ability to recall prevention pop-up messages.

### Outcome Assessments

Table 3 shows the primary outcome measures.

**Table 3. T3:** Primary outcome measures.

Outcome category	Outcome number	Outcome	Description	Measurement time points
Gambling behavior: Money				
	1	Money betted (physical)	Cumulative amount of money physically inserted in the EGM^a^ during the gambling session.	Assessed at the following time points from start of gambling session in the laboratory: [0] T+00:00:00, [1] T+00:10:00, [2] T+00:40:00, [3] T+01:10:00, [4] T+01:40:00, [5] end of gambling session (max T+02:00:00)
	2	Change in money betted (physical)	Change between self-reported measures (past 12 months) and observed data in the laboratory.	Past 12 months; end of the gambling session
Gambling behavior: Time				
	3	Gambling session’s total duration	Time elapsed between the first time the participant puts money in the EGM (T+00:00:00) to the end of the gambling session. Session’s duration is left for the participant to decide. While the participant is told they can play for as long as they like, there is a 2 h limit on the session duration. This limit is hidden from the participant. Session’s duration includes any breaks taken from gambling on the EGM.	Assessed at the end of the gambling session.
	4	Total time effectively spent gambling	Time elapsed between the first time the participant puts money in the EGM (T+00:00:00) to the end of the gambling session, minus breaks taken from gambling on the EGM.	Assessed at the end of the gambling session.
	5	Change in total time effectively spent gambling	Change between self-reported measure (past 12 months) and observed data in the laboratory	Past 12 months; end of the gambling session.
Gambling behavior: Breaks				
	6	Number of breaks taken	Number of breaks taken from gambling on the EGM during the gambling session.	Assessed at the end of the gambling session.
	7	Mean breaks’ duration	Average duration of breaks taken from gambling on the EGM over the gambling session’s total duration.	Assessed at the end of the gambling session.
	8	Total breaks duration	Sum of breaks’ duration taken from gambling on the EGM over the gambling session’s total duration.	Assessed at the end of the gambling session.
	9	Mean time elapsed between breaks	Average time separating any two breaks taken from gambling on the EGM over the gambling session’s total duration.	Assessed at the end of the gambling session.
Gambling behavior: Risk taking				
	10	Number of bets placed	Number of bets placed on the EGM during the gambling session.	Assessed at the following time points from start of the gambling session in the laboratory: [0] T+00:00:00, [1] T+00:10:00, [2] T+00:40:00, [3] T+01:10:00, [4] T+01:40:00, and [5] at the end of the gambling session (max T+02:00:00).
	11	Gambling speed	Number of bets placed on the EGM during the gambling session over a given amount of time (ie, bets/min).	Assessed at the following time points from start of the gambling session in the laboratory: [0] T+00:00:00, [1] T+00:10:00, [2] T+00:40:00, [3] T+01:10:00, [4] T+01:40:00, and [5] at the end of the gambling session (max T+02:00:00).
	12	Gambling intensity (physical)	Money physically inserted in the EGM during the gambling session over a given amount of time (ie, $/min).	Assessed at the following time points from the start of the gambling session in the laboratory: [0] T+00:00:00, [1] T+00:10:00, [2] T+00:40:00, [3] T+01:10:00, [4] T+01:40:00, and [5] end of the gambling session (max T+02:00:00).
	13	Gambling intensity (all)	Money betted on the EGM during the gambling session over a given amount of time (ie, $/min). This is money used to “buy rounds on the EGM,” whether it's money physically inserted in the EGM or money won while gambling and betted again.	Assessed at the following time points from the start of the gambling session in the laboratory: [0] T+00:00:00, [1] T+00:10:00, [2] T+00:40:00, [3] T+01:10:00, [4] T+01:40:00, [5] end of the gambling session (max T+02:00:00).
Cognitions				
	14	Perceived self-control while gambling on EGMs	Participant’s perceived ability to control their gambling behavior (eg, sticking to their predetermined limits) over the gambling session’s total duration. Evaluated with a 7-point Likert scale (1 = “I never had control” to 7 = “I always had control”).	Assessed at the end of the gambling session.
	15	Change in perceived self-control while gambling on EGMs	Change between self-reported measure (past 12 months) and observed data in the laboratory	Past 12 months; end of the gambling session.
	16	Perceived behavioral effectiveness of prevention pop-up messages	Participant’s perceived effectiveness of prevention pop-up messages on modifying their gambling behavior during the gambling session. Evaluated with two 7-point Likert scales about the perceived effects of the prevention pop-up messages on money betted and time spent during the gambling session (1=“lowered gambling behavior a lot” to 7=“heightened gambling behavior a lot”).	Assessed at the end of the gambling session.
Emotions				
	17	General level of fun while gambling on EGMs	Participant’s general enjoyment of gambling on EGMs over the gambling session’s total duration. Evaluated with a 7-point Likert scale (1=“I hated it” to 7=“I loved it”).	Assessed at the end of the gambling session.
	18	Change in general level of fun while gambling on EGMs	Change between self-reported measures (past 12 months) and observed data in the laboratory.	Past 12 months; end of the gambling session.
	19	Psychological reactance to prevention pop-up messages (between group)	Evaluated based on Dillard and Shen [84] method: (1) Induction check (4 items, 7-point Likert scale, 1=“Strongly disagree, 7=“Strongly agree”); (2) Anger (4 items, 7-point Likert scale, 1=“Strongly disagree, 7=“Strongly agree”); (3) Cognitive response (count of negative thoughts in relation to the pop-up messages); and (4) Attitude (7 word pairs, 7-point semantic differential scale).	Assessed at the end of the gambling session.

a EGM: electronic gambling machine.

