### Statistical Methods

Sociodemographic variables, past 12 months of gambling-related variables, and PGSI category will be presented in a table with appropriate central tendency estimates. This table will be divided by assignation group.

A total of 3 statistical models will be used to analyze the outcomes presented in Tables3  4. All these models will control for the time-varying covariate “gains-losses differential” (ie, remaining balance on the EGM at measured time point minus money inserted in the EGM from the start of the study). All models will also test the moderation effect of the following variables: gender (men or women), age (continuous), education (5 categories), and PGSI category (nonproblem, low risk, and moderate risk). Holm-Bonferroni correction [85] will be used to counteract family-wise error rate due to multiple comparisons in each model for each statistically significant categorical variable (ie, time for repeated measures ANCOVAs; moderators with ≥3 categories).

The first model uses ANCOVAs to examine the differences between the two groups at the end of the gambling session on outcome variables 1, 3, 4, 6‐9, 14, 16, 17, and 19, separately.

The second model uses repeated measures ANCOVAs to examine the differences between the two groups at specific time points during the experiment corresponding to the presentation of the prevention pop-up messages in the experimental group. This model is computed on outcome variables 1 and 10‐13, separately.

The third model uses repeated measures ANCOVAs to examine the differences between self-reported measures (past 12 months) and the observed behaviors during the experiment. This model is computed on outcome variables 2, 5, 15, and 18, separately.

Secondary and other outcomes will be documented but will not be statistically compared. Descriptive estimates will be provided for each quantitative variable. Open-ended questions will be analyzed in a manner inspired by the thematic analysis method (see Textbox 3) [86].

Textbox 3.The 5 steps in analysis of open-ended questions.Interviewer’s notes are regrouped in a Microsoft Word document.Raw data is carefully read, both by main author and another member of the research team, to extract categories of similar content.Categories are refined by both coders.Raw data is independently categorized in appropriate categories by both coders.Intercoder agreement is calculated on all categorizations to ensure reliability.

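### For participants stopped at the hidden 2-hour limit, outcome 4 equals 120 minutes minus breaks, so its ANCOVA cannot tell a pause from a choice to gamble less

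*Protocol article*

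**What the plan says.** - **The limit.** The Duplicity section states: "Third, the gambling session’s duration is limited to 2 hours". Breaks are allowed "but are included in the 2-hour time limit". Gambling Session in the Laboratory repeats that "breaks in play, no matter the motive, do not stop the experiment timer regarding the duration limit".
- **At the limit.** The same section plans for the case where "The participant reaches the T+02:00:00 time limit and continues to play". Whether or not the participant accepts the suggested pause, play does not resume. The section also says that participants normally stop by themselves before the limit. It gives no proportion.
- **Outcomes.** Table 3 measures outcome 3 (total duration) from first money inserted to session end, breaks included. Its row describes the length as the participant's own decision and adds: "This limit is hidden from the participant". Outcome 4 runs over the same span "to the end of the gambling session, minus breaks taken from gambling on the EGM". Outcome 8 is the sum of breaks.
- **Intervention.** Textbox 2 shows that every message ends with advice that a break could help. The control arm gets no such messages.
- **Analysis.** Statistical Methods says: "The first model uses ANCOVAs to examine the differences between the two groups at the end of the gambling session". Outcomes 3, 4 and 8 are on that list, each analysed separately. The stated covariate is the time-varying gains-losses differential. Neither this section nor Strengths and Limitations discusses the cap.

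**The concern.** In an unrestricted session a 15-minute pause need not reduce time gambled, because the person can play on afterwards. A participant who reaches the laboratory limit cannot make the time up, so each break minute removes one minute from outcome 4, whatever the person intended. Break advice goes to one arm only, so the effect falls on the experimental arm and points towards benefit.

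Three things are at stake. A fall in outcome 4 could be read as less gambling wanted when it partly mirrors outcome 8. Principal Findings expresses heightened confidence that observed effects carry over to real venues, but a reduction produced by a laboratory limit would not. And the statement that duration is the participant's decision is untrue for those stopped by staff. Outcome 5, the change from self-reported time, is built on outcome 4 and inherits the problem.

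**Working it through.** **Inputs from the protocol.** Cap of 120 min from first money inserted, breaks included; 80 participants, 1:1, so 40 per arm; two-sided 5%. The protocol gives no figure for the share capped or for break time, so both are assumed below.

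**Check of the method.** The plan states 72.34% to 77.66% power for g = 0.58 to 0.62. A two-sample t test with 40 per arm gives 72.6% and 78.2%, so the stated figures reproduce closely.

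**The identity.** Let D be intended active play and B total break time, both in minutes.

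- Outcome 3 = min(D + B, 120)
- Outcome 4 = min(D + B, 120) − B

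If D + B ≥ 120, outcome 3 = 120 and outcome 4 = 120 − B. If D + B < 120, outcome 4 = D and breaks do not matter.

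| Intended play D | B = 0 | B = 5 | B = 10 | B = 15 | B = 20 |
|---|---|---|---|---|---|
| 60 | 60 | 60 | 60 | 60 | 60 |
| 90 | 90 | 90 | 90 | 90 | 90 |
| 110 | 110 | 110 | 110 | 105 | 100 |
| 120 or more | 120 | 115 | 110 | 105 | 100 |

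**Size under assumed inputs.** D has the same distribution in both arms (lognormal, SD of log 0.6). Baseline breaks are exponential with mean 5 min, and the experimental arm has 5, 10 or 20 extra break minutes. Cells show the shortfall in mean outcome 4 and the t-test rejection rate.

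| Controls capped | 5 extra min | 10 extra min | 20 extra min |
|---|---|---|---|
| 6% | 0.2 min; 5% | 0.8 min; 5% | 1.7 min; 6% |
| 14% | 0.8 min; 5% | 1.6 min; 6% | 3.6 min; 9% |
| 34% | 1.8 min; 6% | 3.9 min; 10% | 8.0 min; 27% |
| 53% | 2.7 min; 8% | 5.6 min; 19% | 11.8 min; 66% |

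**Variants.**

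- SD of log 0.7, breaks fixed at 5 min in controls and 15 or 25 min in the experimental arm: 36% capped gives 3.9 or 8.3 min and 9% or 25% rejection; 52% capped gives 5.5 or 11.5 min and 16% or 55%.
- SD of log 0.7, fully exponential break lengths, 2 or 5 extra minutes: at most about 3 min and 4% to 8% rejection at every capped share from about 5% to 53%. With 20 extra minutes and about half capped, the shortfall reaches about 13 min.

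**Does censoring help?** With SD of log 0.7 and 17.5%, 36% or 52% capped, a log-rank test on the active-play clock, censoring those stopped by staff, rejected in 4.4% to 5.5% of replicates. That requires break time to be independent of intended play within arm. With a correlation of −0.5 or +0.5 and 20 extra break minutes, a Cox model gave mean hazard ratios of about 0.90 or 1.15 (36% capped) and 0.83 or 1.20 (52% capped), where 1 is correct.

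**The case against.** A reader might infer that outcome 4 is mismeasured, or that its ANCOVA has an inflated type I error. The documents support neither. A capped participant who pauses does spend fewer minutes gambling in that session, so the recorded value is right. If the messages change neither play nor breaks, the randomised comparison keeps its error rate. The rejections above are misleading only if the result is read as intended, uncapped play, which the protocol does not name as its target.

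A reader might also infer that a reduction in outcome 4 will be largely artefact. That needs heavy capping together with long extra breaks. The protocol calls stopping before the limit normal, and the intervention is at most four 15-second messages with one line of break advice. Outcomes 3, 4 and 6 to 9 will be reported side by side, so part of the mechanism will be visible. For outcome 3, the cap pulls a true difference towards zero, which is conservative.

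These points limit the size but leave the identity standing. A condensed article may leave sensitivity analyses to a fuller plan. This article nevertheless fixes the outcome definition and the ANCOVA, describes duration as freely chosen, and makes a general claim of transfer to real venues.

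**Conclusion.** The point holds as one of interpretation and analysis. For participants stopped at T+02:00:00, outcome 4 carries no information beyond outcome 8, and the planned ANCOVA cannot separate taking a break from choosing to gamble less.

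The size is unknown because the protocol gives neither governing quantity. With no change in intended play, the artefact is negligible at about 6% capped, or at any capped share examined if extra breaks are 5 min or less. It is material only with about a third or more capped and 10–20 extra break minutes. For a third to a half capped that means about 4–13 min and roughly 10–55% rejection, or 66% in the narrower-spread set-up. All these figures rest on lognormal intended play and on break time unrelated to it.

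**What to change.** 1. Label the ANCOVAs of outcomes 3 and 4 as comparisons of time within a 2-hour window. Do not present a reduction in outcome 4 as reduced intended gambling time that transfers to venues. Correct the Table 3 wording on who decides the duration.
2. Beside them, add a censored analysis (Cox or accelerated failure time) of time to voluntary stop on the active-play clock, with participants stopped at T+02:00:00 right-censored at the active time reached. State the assumption that break time is independent of intended play within arm, and specify how the time-varying gains-losses differential enters the model.
3. Report the number stopped at the cap by arm.

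The cost is plan wording and one extra model. Break times and session end are already observed, and the article reports no results yet. The downside is a hazard or time ratio to explain beside the minutes, and an estimate that is only approximately unbiased if break-taking correlates with intended play.
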